**11. Data monitoring plan by study director**

The study directors will keep the data related every 10 cases such as CRF in only restricted computer.

**12. Study goals**

**Primary study goal:**

The procurement rates of histologic cores that the cytopathologist ([name]) considered to be of optimal quality for histological evaluation of the needle gauge

**Secondary study goal:**

Diagnostic performance

Technical failure

Procedure-related adverse events

e.g. Technical failure was defined as any difficulties, including the inability of the needle to exit from the scope channel, mechanical rupture of the needle, and any needle malfunction that required a new needle.

Adverse events were defined as immediate or late bleeding, immediate or late perforation, over-sedation requiring reversal medication, or any other cardiopulmonary distress during or after EUS-guided sampling as observed by the endosonographer or recovery suite nurse or as reported by patients. Acute pancreatitis was defined as serum amylase levels ≥ 3-fold the upper limit of the normal range (>345 g/dL), and for newly developed or worsened pancreatic-type abdominal pain and tenderness with nausea/vomiting, >24 hours after the procedure.

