Similar to EUS-FNA the feasibility and diagnostic yield of EUS-FNB depends on the location, size, and characteristics of target lesions in addition to technical and procedural factors (needle diameter and handling technique, material processing and expertise, and training and interaction between endosonographers and cytopathologists). Furthermore, technical limitations such as mechanical friction of the needle-firing mechanism in larger-caliber needles in the torqued trans-duodenal position, when applied to pancreatic head or uncinated process lesions, may occur with EUS-FNB [10-13]. For this reason, a similarly designed but more flexible FNB device has been developed using a 25-gauge needle platform [14]. Approximately 60% to 70% of diagnosed ductal adenocarcinomas occur in the pancreatic head or uncinated process, underscoring the need for an effective trans-duodenal approach. Furthermore, blood and cellular debris contamination complicate cytopathological interpretation, a common occurrence with the widely used 22-gauge needle.[15] In addition, it is often difficult to penetrate a calcified solid mass with a 22-gauge needle.[15] We hypothesized that a 25-gauge needle would provide an appropriate specimen while more easily penetrating solid pancreatic masses.

However, it is unclear whether the theoretical benefit of 25-gauge needles for EUS-FNB actually results in a higher procurement rate of high-quality histologic core samples compared to 22-gauge needles. Furthermore, no study has evaluated histologic core procurement rates of 25-gauge needles. Therefore, the aim of this study was to compare the efficacy of the recently developed 25-gauge EUS-FNB device to 22-gauge EUS-FNB for obtaining histologic core tissues in order to assess solid pancreatic masses.

[figure not shown]

Figure 1. 25-gauge Ultrasound biopsy needle (EchoTip® ProCore™ High Definition Ultrasound Biopsy Needle, Cook Medical Inc, Bloomington, IN)

Figure 2.

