All patients will undergo EUS-FNB with 22-gauge (Echotip ProCore; Cook Endoscopy Inc, Limerick, Ireland) and 25-gauge (Echotip ProCore; Cook Endoscopy Inc, Limerick, Ireland) needles subsequently for the same pancreatic lesion; the procedures will be performed by an experienced echoendoscopist ([name]) with a current volume of 750 EUS cases per year, including 150 or more FNA/FNB, using a well-established technique [17]. The FNB device will be made of a 140-cm stainless steel with a 5.2 F shaft ending with a beveled tip 4 mm in length within a spiral steel sheath surrounded by a Teflon cover. All procedures will be performed with a linear array echoendoscope (Olympus UCT 260, Olympus Co., Tokyo, Japan). After visualizing the target lesion in the endosonographic plane, the echoendoscopist will use color Doppler to identify the optimal position for puncture without intervening vessels between the needle and target lesion. The needle will be inserted into the target tissue under EUS guidance via the duodenum for pancreatic head and uncinate masses and via the stomach for pancreatic body and tail masses. Once the lesions will be well penetrated with the needle, the stylet will be removed; a 10-cm^3^ suction syringe will be applied to the needle hub, and 10 uniform back-and-forth movements will be performed within the lesion during each needle passage. The needle will be then withdrawn into the spiral steel sheath and detached from the echoendoscope. After two individual punctures, the first needle will be withdrawn into the catheter and removed; the procedure will be repeated in same fashion with the second needle. The FNB needle sequences will be randomly assigned in a 1:1 proportion based on a computer-generated random order (22- or 25-gauge first), and two punctures will be conducted for each needle respectively. The allocation sequence will be concealed using opaque sealed envelopes, and neither the cytopathologist nor the patients will be unaware of the treatment allocation.

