**13. Statistical analysis**

Descriptive statistics were provided for binary and continuous variables using incidence frequency (%) and mean ± standard deviation and range. McNemar tests were used to compare binary variables, and two-sample *t*-tests were used to compare continuous variables. Sensitivity, specificity, diagnostic accuracy, positive predictive value (PPV), and negative predictive value (NPV) of each needle were calculated based on per protocol analysis. Two-sided *P*-values were calculated and significance was accepted at 5%. All statistical analyses were performed using PASW Windows, version 18.0.0 (SPSS Inc., Chicago, IL, USA).

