**Fators related intervention**

Access route

Number of passes for diagnosis

Puncture with stylet

Number of to-and-fro movements within the lesion

Use of the stylet to harvest the core sample from the needle

Presence of histologic core

Technical difficulty

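### Technical failure is defined to include any difficulty, so the tested needle comparison could reflect unblinded ratings; test the three listed device events and describe the rest

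*Protocol*

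**What the plan says.** Section 12 of the protocol lists technical failure as one of three secondary goals. The definition opens with "Technical failure was defined as any difficulties, including the inability of the needle to exit from the scope channel" and continues with "mechanical rupture of the needle, and any needle malfunction that required a new needle". The governing term is any difficulty, and the three device events come after the word including.

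Section 12 names no assessor for technical failure. The adverse-event definition beside it does name observers: the endosonographer, the recovery nurse and the patients.

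In Section 10, "the procedures will be performed by an experienced echoendoscopist", and each patient is punctured with both needles in randomised order. The blinding sentence reads "neither the cytopathologist nor the patients will be unaware of the treatment allocation". It carries a double negative, but the same section describes the cytopathologist as blinded to needle type and sequence, so the intention is clear. The operator is not mentioned as blinded.

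Section 15 lists "Technical difficulty" among the intervention factors. It has no item called technical failure.

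Section 13 says "McNemar tests were used to compare binary variables", with two-sided significance at 5%.

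Section 3 states the expectation "We hypothesized that a 25-gauge needle would provide an appropriate specimen while more easily penetrating solid pancreatic masses". It also says that calcified masses are often hard to penetrate with a 22-gauge needle.

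**The concern.** A failure outcome used to compare two devices should turn on events that a second person could confirm. Under the definition as written, a pass that felt stiff counts the same as a ruptured needle. If the person who records it can see the gauge, and the protocol has already said which gauge should penetrate more easily, the comparison is open to expectation. Randomising the needle order does not help, because the gauge is visible whichever needle comes first.

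What is at stake is a sentence in the trial report saying that one needle had significantly more technical failures. A reader would take that to mean needles that jammed, broke or were replaced. The definition permits the sentence when none of these happened.

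**Working it through.** **Inputs from the protocol.** 56 evaluable pairs, raised to 66 for 15% dropout (Section 5); McNemar test, two-sided 5% (Section 13). The pair count reproduces: 56 / (1 − 0.15) = 65.9, rounded up to 66. The protocol gives no rate for technical failure or difficulty, so there is no stated figure to check. The two steps below are illustrations.

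**Step 1: how few ratings are enough.** Assume one yes/no result per needle per patient. With b patients showing a difficulty on one needle only and none on the other needle only, the exact two-sided McNemar P is 2 × 0.5^b.

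- b = 5: 2 × 0.5^5 = 0.0625, not significant.
- b = 6: 2 × 0.5^6 = 0.031, significant.
- Share of patients: 6/66 = 9.1%; 6/56 = 10.7%.

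The protocol does not say whether the exact test is meant. With the uncorrected asymptotic statistic (b − c)²/(b + c), four against none gives 16/4 = 4.0, which already exceeds 3.84.

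Six against none is the smallest wholly one-sided split that reaches 5% in any exact McNemar test. It shows the threshold, not how likely it is to be crossed here.

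**Step 2: how often labelling alone would produce a difference.** Every rate here is an assumption. Let the true rate of the three listed events be the same for both needles, o = 2% or 5%. Let other difficulties be noted in a proportion s of uses, with results independent within patient. The recorded rate is then p = o + (1 − o) × s.

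Worked case, o = 2%, s = 15% for 22-gauge and 5% for 25-gauge:

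- 22-gauge: 0.02 + 0.98 × 0.15 = 0.167
- 25-gauge: 0.02 + 0.98 × 0.05 = 0.069
- discordant, 22-gauge only: 0.167 × 0.931 = 0.155
- discordant, 25-gauge only: 0.069 × 0.833 = 0.057

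Summing exact McNemar rejections over the possible discordant counts in 66 pairs gives a 32% chance of a significant difference. The full set for 66 pairs:

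| What counts as failure | o = 2% | o = 5% |
|---|---|---|
| Listed events only | 0.1% | 1.4% |
| Plus difficulty, 5% on each needle | 2.0% | 2.4% |
| Plus difficulty, 10% v 5% | 9.5% | 8.3% |
| Plus difficulty, 15% v 5% | 32% | 26% |
| Plus difficulty, 20% v 5% | 60% | 51% |
| Plus difficulty, 25% v 5% | 83% | 74% |

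With 56 pairs the last four rows fall to 7.7%, 26%, 51% and 75% at o = 2%, and to 6.8%, 21%, 43% and 66% at o = 5%.

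The second row matters: a broad definition applied evenly does not inflate the error rate. The problem arises when difficulty is noted unevenly. The test cannot then tell a real handling difference from expectation.

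**The case against.** **The three examples set the sense.** The outcome is called failure and every example is a concrete device event, so a sensible reader would look for events of that kind. A threshold for other difficulties could sit in case-report instructions or an analysis plan that is not shown. This is fair as to intention. The protocol nevertheless states a rule, and the rule as worded is open. Narrowing it later would change an outcome already defined.

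**The assessor is not the operator on the face of the text.** A reader might infer that the protocol appoints the unblinded operator as judge. It does not; it names no one. The operator is the natural source, as the only person handling both needles, but that is an assumption.

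**There may be no separate difficulty field.** A reader might infer that failure and difficulty are recorded separately and then merged without need. Section 15 lists only a difficulty item, which may itself be the source of the outcome. A separate record of failure is therefore not established, and the repair needs a new data item.

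**The hypothesis is not proof of bias.** It shows a direction of expectation. Section 3 itself goes on to call the benefit of the 25-gauge needle unclear. Nothing in the documents shows biased rating.

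**A narrow definition loses something.** An intact needle that leaves the scope but cannot enter the lesion is a meaningful failure, and Section 3 makes penetration part of the case for the finer gauge. This stands as a real cost of the fix.

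**Conclusion.** The definition is stated but too open for an outcome that is to be tested between needles. Unlisted and unverifiable difficulties count fully as failures and could carry the comparison on their own. That they would be rated by someone aware of the gauge is an inference from the single operator and the blinding statement.

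The size cannot be estimated from the documents. Six one-sided ratings among 66 pairs are enough for exact P = 0.031. Under the assumed uneven labelling, the chance of a significant difference with equal true failure runs from about 8% to 83% for 66 pairs. Those figures depend wholly on the assumed rates.

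A reader might go further and call the outcome undefined, or doubt the trial's main result. Neither follows. A definition exists, and the primary outcome is judged by a cytopathologist described as blinded to needle type and sequence, so it is unaffected. This is a cheap improvement to one secondary outcome.

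**What to change.** In Section 12, define the tested outcome as the occurrence of any of the three events already listed: the needle cannot exit the scope channel, the needle ruptures mechanically, or a malfunction requires a new needle. Add a matching technical-failure item to Section 15, recorded for each needle, beside the existing difficulty item.

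Report every other difficulty separately and descriptively for each needle, labelled as an unblinded operator rating. Name failure to penetrate the lesion with an intact needle explicitly in that report, so that it is not lost.

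The cost is a revised sentence and one data item. There will be fewer technical-failure events, so the test will have less chance of showing a difference, and penetration problems will be described but not tested. No part of the procedure or of patient care changes.

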**10. Study procedure**

This study will be a randomized, double-blinded, prospective study of 66 consecutive patients with pancreatic solid masses who will be referred to our medical center for EUS-FNB during 1 year after IRB approval in Severance hospital. Patients will be eligible for the study based on the following criteria: suspected solid pancreatic masses based on clinical work up and image modality that required cytopathological confirmation. Exclusion criteria will include: (a) cystic pancreatic lesions without the evidence of solid component suspected with malignant transformation; (b) hemodynamical instability; (c) severe coagulopathy (international normalized ratio > 1.5 or platelet count < 50,000 cells/cubic millimeter [cmm^3^]); (d) inability to suspend antithrombotic therapy; (e) pregnancy; and (f) refusal to provide informed consent or participate in the study. All patients will undergo EUS-FNB under moderate-to-deep balanced propofol sedation based on midazolam according to current guidelines [16]. Patients will be monitored for immediate post-procedural adverse events for least 4 hours after completion of the procedure and will be followed up for up to 30 days to detect late adverse events; non-surgical patients received clinical follow-ups for at least 6 months.

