**Physical exam after intervention**

New or increased upper abdomen or epigastric pain, back pain, and epigastric tenderness

Temperature

Blood pressure

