**Laboratory findings after intervention**

CBC

Routine chemistry including amylase and lipase

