**Procedure related complication**

**Presence of histologic core**

**Histological diagnostic categories**

**Final histologic diagnosis**

**Final clinical and pathologic diagnosis as reference**

**Quality of histologic specimens**

**16. Predictable adverse events**

Adverse events will be defined as immediate or late bleeding, immediate or late perforation, over-sedation requiring reversal medication, or any other cardiopulmonary distress during or after EUS-guided sampling as observed by the endosonographer or recovery suite nurse or as reported by patients.

Acute pancreatitis was defined as serum amylase levels ≥ 3-fold the upper limit of the normal range (>345 g/dL), and for newly developed or worsened pancreatic-type abdominal pain and tenderness with nausea/vomiting, >24 hours after the procedure.

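### The adverse-event definition is a closed list that, read literally, omits procedure-related infection or fever and significant pain short of pancreatitis, although temperature and pain are recorded

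*Protocol*

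**What the plan says.** Section 12 lists "Procedure-related adverse events" among the secondary goals and defines them in the same place: "Adverse events were defined as immediate or late bleeding, immediate or late perforation, over-sedation requiring reversal medication, or any other cardiopulmonary distress", observed by staff or reported by the patient during or after sampling. The next sentence defines one further condition: "Acute pancreatitis was defined as serum amylase levels ≥ 3-fold the upper limit of the normal range", together with new or worse pancreatic-type pain and tenderness with nausea or vomiting, more than 24 hours after the procedure.

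Section 16, headed "Predictable adverse events", restates the list in the future tense ("Adverse events will be defined as immediate or late bleeding, immediate or late perforation, over-sedation requiring reversal medication", then the cardiopulmonary item) and repeats the pancreatitis criteria.

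Section 15 sets out what is recorded after the intervention: temperature, blood pressure, "New or increased upper abdomen or epigastric pain, back pain, and epigastric tenderness", a blood count, and "Routine chemistry including amylase and lipase". It also lists an item for procedure-related complications, with no definition and no categories. Under section 10, patients are observed for at least 4 hours and then "will be followed up for up to 30 days to detect late adverse events".

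**The concern.** The data collection is wider than the definition. Temperature and pain are recorded after the procedure and late events are sought for a month, but the definition gives two kinds of finding no route into the endpoint: fever or infection, and significant pain that falls short of pancreatitis. A definition that leaves out categories can only lose events, so any error in the rate runs downward.

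What is at stake is a secondary, descriptive rate per patient. Each patient is to receive both needles, with two punctures each, in one session (section 10). The needle comparison on histologic core procurement, which is the primary goal, is not affected. But the sample is small, so how one or two patients are classified shows in the reported figure. What counts as an event also shapes what is recorded from the first patient onward, so the analysis cannot reliably repair it later.

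**Working it through.** No figure in the protocol depends on this definition, so there is none to reproduce. The check sets the passages side by side and then works out the weight of one patient.

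**Step 1: is the list closed?** Sections 12 and 16 use the same four items: bleeding, perforation, over-sedation needing reversal, and other cardiopulmonary distress. The open phrase in the fourth item applies only to cardiopulmonary distress. In the same part of section 12, technical failure is defined openly, as any difficulty, with examples. The adverse-event sentence has no such wording.

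**Step 2: which findings reach a definition?**

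| Finding after the procedure | Recorded under section 15 | Counts under sections 12 and 16, read literally |
|---|---|---|
| Bleeding or perforation, immediate or late | Through the complication item | Yes, listed |
| Over-sedation needing reversal, other cardiopulmonary distress | Through the complication item | Yes, listed |
| Acute pancreatitis meeting the stated criteria | Amylase, lipase, pain | Yes on the natural reading: it has event criteria directly after the list, although the list does not name it |
| Infection or fever | Temperature, blood count | No |
| Significant pain, amylase below 3-fold the upper limit | Pain, amylase | No |
| Significant pain, amylase raised, no nausea or vomiting | Pain, amylase | No, since the pancreatitis criteria require those symptoms as well |

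**Step 3: does the complication item close the gap?** Section 15 lists it without content. It may take over the list in sections 12 and 16, or it may be a free judgement under a second term. The protocol does not say which, nor how the item feeds the secondary endpoint.

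**Step 4: weight of one patient.** Inputs: 66 planned patients and 56 before the allowance for dropout (section 5).

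- One patient of 66: 1/66 = 1.5 percentage points.
- One patient of 56: 1/56 = 1.8 percentage points.
- Two patients of 66: 2/66 = 3.0 percentage points.

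These are the weights of hypothetical patients, not estimates of bias. The protocol gives no frequency for infection, fever or isolated pain, so the expected number missed cannot be calculated.

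**The case against.** The strongest reply is that the protocol is wider in practice than the list sentence. Temperature, pain and laboratory values are collected, follow-up runs to day 30, and the complication item is not restricted to named categories. The heading of section 16 speaks of predictable events, which suggests a list of what is expected rather than a limit on what may count. An investigator could record an infection as a complication and report it. This part stands: under-counting is a risk of the wording, not something the documents show. It does not remove the point, because both sections state what adverse events are defined to be, and nothing connects the complication item to the endpoint.

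Three stronger readings are tempting, and the documents do not support them.

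- **That pancreatitis is excluded.** The list does not name it, but its criteria follow at once in section 12 and again under the adverse-event heading in section 16, and amylase and lipase are measured afterwards. The natural reading is that it counts. Only the explicit link is missing.
- **That a re-admitted patient is never an event.** The protocol does not mention re-admission. Late bleeding, late perforation, cardiopulmonary distress and pancreatitis are covered, so a re-admission would be missed only if its cause lay outside these.
- **That the rate is no longer comparable with a benchmark of 0% to 3%.** Sections 3 and 9 give that range as background for EUS-FNA, not for the biopsy needles under study, and no comparison with it is planned. How the cited sources defined adverse events cannot be checked here.

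**Conclusion.** The point holds as a defect of definition. Sections 12 and 16 fix the adverse-event endpoint by an enumerated list plus criteria for acute pancreatitis. Applied as written, they leave out procedure-related infection or fever and significant pain that does not meet the pancreatitis criteria, although the signs of both are recorded.

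The direction of any error is known: the rate can only be too low. Its size is not known, beyond 1.5 percentage points for each missed patient if all 66 are analysed. The conclusion assumes that the definition is applied literally and that the complication item adds nothing to it. If that item is used as an open field and counted in the endpoint, the gap narrows or closes, but the protocol does not say so.

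The primary comparison is untouched. The change is still worth making, because it corrects a stated rule for a secondary safety endpoint at little cost.

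**What to change.** In sections 12 and 16, replace the closed list with one open definition, identical in both: any event judged related to the procedure or the sedation, from the start of sedation to day 30, including the items now listed, acute pancreatitis (named explicitly), infection or fever, and significant pain. The study team should state in advance what makes fever or pain count.

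Two features matter. Relatedness must stay in the definition; otherwise complications of later surgery, or progression of the disease within 30 days, would count as biopsy events. The window must open at the start of sedation rather than at puncture, so that sedation events before the needle is inserted are not lost.

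State in section 15 that the complication item uses this same definition, and report the overall rate and the rate in each category.

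The cost is two reworded paragraphs and one cross-reference; the fields and the 30-day follow-up already exist. Relatedness must be judged for each event, and the reported rate may be slightly higher.
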